#### High intensity interval training

HIIT will be performed on a bicycle ergometer with high intensity interval and rest intervals alternated, to improve the cardiorespiratory fitness. The training will start with a 10-min warm-up on the bicycle on light-to-moderate intensity, then participants will start the HIIT training (Table 1b). The intervention will end with a cool down period of 5 min bicycling and 5 min of muscle stretching and relaxation (see Additional file 2 TIDieR Checklist).

During the intervention period and during the 16 weeks pre- and post-intervention participants are asked not to follow an exercise program outside this study, and to keep their level of care constant during this period when possible. Usual medical care is continued, including new treatments when the health situation of the patient changes.

#### Training intensity

For the PRT group, to determine muscle strength the 1RM of every exercise performed during the progressive resistance training will be determined in kg. For the HIIT group, cardiorespiratory fitness will be determined during a cardiopulmonary exercise test (CPET). Outcome measures are peak oxygen consumption (VO_2_peak) in oxygen per ml/min/kg, peak heartrate (HR peak) in beats per minute and peak load (Wpeak) in Watt. Muscle strength and cardiorespiratory fitness will be re-examined at week 8 of the intervention period, to optimize training intensity (Table 1).

### Outcome measures

Measurement will take place at baseline (week 0), extended baseline (week 16), post-intervention (week 32) and at follow-up (week 48) (Table 2).

**Table 2 Tab2:** Schedule of enrollment and measurements

	**Enrollment**	**Baseline**		**Intervention period**	**Post-intervention**	
Week no:	-1	0	16	24	32	48
**Informed consent**	X					
**Screening**	X					
**Sociodemographic and clinical characteristics**		X				
**Neurodegeneration**						
Imaging		X	X		X	X
Blood sampling		X	X		X	X
**Patient functioning**						
• Mobility		X	X		X	X
• Dexterity		X	X		X	X
• Cognition		X	X		X	X
• Balance		X	X		X	X
• Disease		X	X		X	X
• Psychosocial		X	X		X	X
• Global perceived effect					X	X
**Cardiovascular risk factors**		X	X		X	X
**Activity level during follow-up**						X

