**Methods:**

In a single-blinded phase II clinical trial with an extended baseline period, 60 people with PMS will be randomly assigned to PRT or HIIT. The participants should have had a relapse onset of MS with confirmed disease progression, however still ambulatory. The duration of the study is 48 weeks, consisting of 16 weeks baseline period (no intervention), 16 weeks intervention and 16 weeks follow-up. Patient-tailored training will be performed 3 times per week for one hour in groups, led by an experienced physiotherapist. The primary outcome measure is neurodegeneration, measured as whole brain atrophy on magnetic resonance imaging (MRI). Secondary outcome parameters will include other biomarkers associated with neurodegeneration (i.e. regional brain atrophy, lesion load, white matter integrity, resting state functional connectivity, blood biomarkers (brain derived neurotrophic factor (BDNF) and serum neurofilament light (sNFL)), patient functioning (physical and cognitive) and cardiovascular risk factors.

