## Methods/design

### Design and setting

A single-blind monocenter randomized phase II trial with extended baseline will be conducted from 2020 till 2023 at the MS Center Amsterdam (MSCA), The Netherlands. MSCA is embedded in the Amsterdam UMC, location VUmc, and is a specialized center for MS care, research and education. In an extended baseline design, participants function as their own control reducing variance and increasing power. During intake participants will be assessed for eligibility for inclusion. In case of inclusion, participants will be scheduled for two baseline measurements sixteen weeks apart. After the second baseline measurement participants will be randomized to either the PRT or HIIT group. Measurements will be repeated post-intervention and after a 16-week follow-up period.

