##### Domain specific perceived effect

The global changes over a specified time window will be measured using a single question scored on a 7-point scale, also known as the global perceived effect [64, 65]. Domain specific effect for muscle strength and cardiorespiratory fitness will be determined.

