#### Additional objectives

Longitudinal assessment of change in the different outcome measurements will be determined using a linear mixed model over four different time points. The relationship between (change in) patient functioning measures and (change in) neurodegeneration will be assessed using multiple regression analyses. The relative responsiveness of the various neurodegenerative biomarkers will be analyzed by relating the smallest real difference to the minimally important change of the outcome measures and comparing the area under the receiver operation characteristics curves [74]. Domain-specific patient perceived effect parameters will be used as an anchor. To analyze the effects on cognitive performance, a Reliable Change Index (RCI) will be calculated based on the mean and standard deviation of the healthy controls to adjust for learning effects [75]. An RCI of ±1.64 (90%) will be considered a significant improvement/decline.

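### Perceived effect, the anchor for the responsiveness analysis, is not rated at week 16, so no patient rating of change covers the pre-training control interval

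*Protocol article*

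**What the plan says.** Under Patient functioning in Table 2 (Schedule of enrollment and measurements), mobility, dexterity, cognition, balance, disease and psychosocial measures are marked at weeks 0, 16, 32 and 48. The row "Global perceived effect" is marked at weeks 32 and 48 only. Imaging and blood sampling are marked at all four visits.

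The section Domain specific perceived effect describes the instrument: "The global changes over a specified time window will be measured using a single question scored on a 7-point scale". It is to be determined for two domains, muscle strength and cardiorespiratory fitness. The article does not give the time window.

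The Additional objectives paragraph of the statistical analysis compares biomarkers through the smallest real difference, the minimally important change and ROC areas, and adds: "Domain-specific patient perceived effect parameters will be used as an anchor".

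On the control condition, Design and setting states: "In an extended baseline design, participants function as their own control". The abstract describes the 48 weeks as "consisting of 16 weeks baseline period (no intervention), 16 weeks intervention and 16 weeks follow-up". There is no untrained arm of people with MS. Randomization and blinding states that participants are not blinded and learn their programme at the first training session.

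**The concern.** An own-control design works only for measures that are read over the control interval. A rating of change cannot be made at week 0, but it can be made at week 16, and that visit already takes place. Two consequences follow from leaving it out.

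- **As an outcome.** One additional objective is whether training improves patient functioning, and perceived effect is listed under that heading. Participants know they are training, and some will report improvement for that reason alone. The share improved at week 32 cannot be set against the share who would have said the same over an untrained 16 weeks before training.
- **As an anchor.** Imaging and blood are measured at both ends of weeks 0-16, but nothing classifies that interval as changed or not. One of the three measured intervals, and the only one untouched by training, drops out of the anchor-based ROC and minimally important change analysis.

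It also matters how many ratings week 32 leaves on the unchanged side, because a small reference group makes ROC areas imprecise and the ranking of biomarkers unstable.

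**Working it through.** **Schedule set against design**

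| Interval | Study training | Biomarkers at both ends | Perceived effect at the end |
|---|---|---|---|
| Weeks 0-16 | none, before training | yes | no |
| Weeks 16-32 | yes | yes | yes |
| Weeks 32-48 | none, after training | yes | yes (window not given) |

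The gap is in the first row. This step needs no arithmetic.

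**The plan's own figure.** The article gives no precision target for the responsiveness analysis. Its sample size concerns the primary outcome and reproduces: effect size 0.3/0.5 = 0.6; a two-sided paired t-test with 24 participants has power 0.804; 24/0.85 = 28.2, so 29 per group against 30 planned. The point here does not depend on it, except that 60 participants with 15% drop-out leave 60 × 0.85 = 51 completers.

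**Precision of an ROC area (illustration).** The article gives neither an expected ROC area nor a distribution of ratings. Assumed: area A = 0.70; ratings split into improved (n1) and not improved (n0); all ratings independent. The Hanley-McNeil formula is

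SE² = [A(1−A) + (n1−1)(a−A²) + (n0−1)(b−A²)] / (n1·n0), with a = A/(2−A) and b = 2A²/(1+A).

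At A = 0.70: A(1−A) = 0.21, a−A² = 0.5385−0.49 = 0.0485, b−A² = 0.5765−0.49 = 0.0865.

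*Week 32 alone, 51 ratings:*

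- 90% improved (46 v 5): SE 0.109
- 80% improved (41 v 10): SE 0.084
- 70% improved (36 v 15): SE 0.076
- even split (26 v 25): SE 0.073

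*Weeks 32 and 48, as already scheduled, with 80% improved at week 32:*

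- 30% improved at week 48 (41+15 = 56 v 46): SE 0.051
- 60% improved at week 48 (41+31 = 72 v 30): SE² = (0.21 + 71×0.0485 + 29×0.0865)/2160 = 0.00285, SE 0.053
- 80% improved at week 48 (41+41 = 82 v 20): SE 0.059

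*Week 16 added to the middle case, 20% improved (10 v 41):* 72+10 = 82 v 30+41 = 71. SE² = (0.21 + 81×0.0485 + 70×0.0865)/5822 = 0.00175, SE 0.042.

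The 95% half-width falls from 1.96×0.053 = 0.10 to 1.96×0.042 = 0.08. Going from 102 to 153 independent ratings would by itself shrink the SE by √(102/153) = 0.82, from 0.053 to about 0.044. Most of the gain is therefore volume and little is better balance. Because each person contributes several ratings, the true gain is probably smaller.

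**The case against.** The strongest reply is that the schedule already contains a rating after a period without training. The intervention ends at week 32, the next 16 weeks are follow-up, and the article says of outside exercise: "During the intervention period and during the 16 weeks pre- and post-intervention participants are asked not to follow an exercise program outside this study". A reader might infer from Table 2 that perceived effect has no untrained reading at all. That goes too far: if the week-48 question refers to weeks 32-48, it is one. What it cannot be is a pre-training control. Participants have just finished a programme, so the interval mixes loss of training effect with carry-over.

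A reader might also infer that almost nobody will be rated unchanged. The article does not support this, because it gives no distribution of ratings. Each programme chiefly targets one of the two rated domains, so 'no change' answers for the other domain are plausible. The calculation agrees that balance is not the main issue: at week 32 alone, moving from 41 v 10 to an even split improves the SE only from 0.084 to 0.073, and the scheduled week-48 ratings bring it to 0.051-0.059. This part of the objection stands.

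Finally, cut-points, pooling of intervals and the sample for the smallest real difference may sit in the full protocol or analysis plan. The article does not say that perceived effect must define who is stable, so no fault is claimed there. The missing week-16 rating is different, because the article's own schedule fixes it.

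**Conclusion.** The point holds in a limited form. Perceived effect is both a patient-functioning outcome and the responsiveness anchor, and it has no reading over weeks 0-16, the only pre-training control interval. Rated change under unblinded training has no pre-training comparator, and run-in biomarker change is shut out of the anchor-based analysis. Both follow from the schedule without numerical assumptions.

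The effect on precision is modest and illustrative: SE about 0.053 with weeks 32 and 48, about 0.042 with week 16 added. It rests on an assumed area of 0.70, 51 completers, 80%, 60% and 20% improved at weeks 32, 48 and 16, and independence between a person's ratings. Week 32 alone may leave few unchanged ratings, but how few cannot be derived from the article.

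This is a cheap improvement to secondary objectives. The primary analysis of percentage brain volume change is unaffected.

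**What to change.** - Ask the same 7-point questions for muscle strength and cardiorespiratory fitness at the week-16 visit, with weeks 0-16 as the stated window. Randomization follows that visit, so the rating can be completed before allocation is disclosed.
- State matching windows for the later ratings: weeks 16-32 at week 32 and weeks 32-48 at week 48.
- Report the share improved over training next to the share improved over the run-in.
- Include the run-in ratings, with the biomarker changes over the same weeks, in the ROC and minimally important change analysis, clustered by participant.

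The cost is a few single items at an existing visit and a cluster adjustment in the analysis. The change should be made early, because a participant who has passed week 16 cannot validly supply the rating afterwards.

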**Training Intensity**						
1RM		X	X	X^a^	X	X
CPET		X	X	X^a^	X	X

^a^ Study group dependent

#### Primary outcome measure: percentage brain volume change

The primary outcome measure of this study is PBVC measured on MRI. A longitudinal assessment of whole brain atrophy will be determined using a high resolution T1-weighted image (i.e. three-dimensional magnetization-prepared rapid acquisition with gradient echo). Whole brain atrophy is an overall measure of neurodegeneration in MS [38, 39]. A valid software tool SIENA (part of FSL, https://fsl.fmrib.ox.ac.uk/fsl/fslwiki/SIENA) is available to determine PBVC automatically [40].

#### Other neurodegeneration biomarkers

##### Imaging

The following imaging markers will be determined:
Grey matter, white matter, subcortical volumes and cortical thickness (as measured with respectively SIENA and FIRST (from fsl) and Freesurfer) [41].Lesion load using a fluid-attenuated inversion recovery (FLAIR) image [42].White matter integrity measured with DTI [41].rsFC will be calculated. In the proposed study we will focus on the rsFC in the sensorimotor network and DMN, which both can be determined reliably in people with MS [43]. Previous exercise intervention studies found changes in rsFC of the sensorimotor network after an exercise intervention [24, 26]. In older healthy individuals also changes in DMN are demonstrated [44, 45]. In people with MS the rsFC in the DMN is lower compared to healthy controls [20]. In physically active people with MS rsFC in the DMN is higher [17].

##### Blood sampling

Blood biomarkers including BDNF and serum Neurofilament Light (sNFL), will be assessed. Neurofilaments are the major component of axonal cytoskeleton proteins and during axonal damage, neurofilaments are released in the extracellular fluid [46]. sNFL gives an indication of the degree of axonal damage. Beside this, additional blood biomarkers will be determined. The field of research on MS and blood biomarkers is evolving rapidly. Based on these developments it will be determined in a later stage. To determine immunological responses to exercise immune cell profiles will be determined with a combination of flow cytometry by time of flight (CyTOF) mass cytometry and multi-parameter flow cytometry.

#### Patient functioning

##### Mobility

Different aspects of walking will be assessed. First, the energy cost of walking will be determined (6MWTec). 6MWTec is a measure of oxygen consumption per meter during walking, which is strongly associated with daily activity and perceived fatigue in MS [47]. Oxygen consumption will be determined during 6 min of walking with breath-by-breath gas exchange measurements. The last 3 min of the test are used to determine oxygen consumption, because steady state oxygen consumption is then assumed. Second, the 25-ft timed walk test (25 ft. TWT) will be performed. Participants will have to perform the 25 ft. TWT two times as fast as possible and two times on comfortable walking speed [48, 49]. Third, the patient-reported Multiple Sclerosis Walking Scale (MSWS-12), will be filled in [50].

##### Dexterity

Manual ability of both hands will be measured with the nine-hole peg test (9-HPT) [51].

##### Cognition

The Brief International Cognitive Assessment for MS (BICAMS) will be used to examine information processing speed and immediate verbal and visual recall [52]. The BICAMS consists of the Symbol Digit Modalities Test (SDMT), California Verbal Learning Test-II (CVLT-II) and the Brief Visuospatial Memory Test-Revised (BVMT-R). Parallel versions will be used to avoid learning effects. Fifteen healthy controls will also be included and followed over the same 48-week time span to be able to correct for learning effects in the analysis.

##### Balance

The Berg Balance Scale (BBS) will be used to assess balance [53, 54]. In this 14-item scale a rater scores different balance tasks, from sitting without support till standing on one leg, on a 0–4 scale. The total score will be between 0 and 56, a higher score representing better balance.

##### Disease severity and impact

A disease specific measurement of disability in MS is the EDSS combing impairment(s) in functional systems (pyramidal, cerebellar-, brain stem-, sensory-, bowel & bladder-, visual-, cerebral-, and other systems) and impairment in walking [34]. Disease impact will be measured with a 29-item patient-reported Multiple Sclerosis Impact Scale (MSIS-29) [55].

##### Psychosocial

Depression and anxiety will be assessed with the HADS [37, 56]. Resilience, the ability to bounce back from challenges occurring in life will be measured with the Connor Davidson Resilience Scale (CD-RISC25), a 25-item patient-reported outcome measure [57]. Fatigue will be determined using the Checklist Individual Strength-20r (CIS-20r), a patient-reported questionnaire [58, 59]. Quality of life will be assessed with the Short-Form health survey-36 (SF-36) [60, 61]. Exercise self-efficacy, confidence in performing exercise will be assessed with the EXercise Self-Efficacy scale (EXSE) [62, 63].

##### Domain specific perceived effect

The global changes over a specified time window will be measured using a single question scored on a 7-point scale, also known as the global perceived effect [64, 65]. Domain specific effect for muscle strength and cardiorespiratory fitness will be determined.

#### Cardiovascular risk

People with MS often have a worse cardiovascular risk profile compared to healthy individuals [66]. The unfavorable cardiovascular risk profile might be explained by a sedentary lifestyle common in MS [67]. In people with PMS the cardiovascular risk profile is even worse compared to people with relapse-remitting MS, but this might be explained by a further decline in mobility and daily functioning in the more progressive stages of the disease [68]. Exercise interventions might be beneficial for both patient functioning and cardiovascular risk factors [69, 70]. Studies do indicate that a higher cardiovascular risk is associated with higher lesion load, more brain atrophy and more disability progression [68, 71, 72]. The following cardiovascular risk factors will be determined; body weight, height, body mass index, % body fat, blood pressure, High-Density Lipoprotein (HDL), Low Density Lipoprotein (LDL), cholesterol, C-reactive Protein (CRP) and Hemoglobin A1c (HbA1c).

#### Demographic and clinical characteristics

Demographic and clinical characteristics will be determined at baseline. The following demographic characteristics will be determined: age, sex, educational level, level of physical activity with the International Physical Activity Questionnaire (IPAQ). The following clinical characteristics will be documented: comorbidities measured with CIRS, year of diagnosis, disease duration, use of medication, use of walking aid, level of education, work and hours of work per week.

#### Therapy adherence

Therapy adherence will be monitored. Presence or absence during training sessions will be documented. In the HIIT group the number of performed intervals and intensities will be documented and in the PRT group, the number of repetitions and sets will be documented as well as the weights.

### Statistical analysis

Statistical analysis will be performed using IBM SPSS (Chicago, Illinois) and/or R (Auckland, New Zealand). Nominal data will be presented as frequencies (n) and percentages (%). Ordinal and interval data will be presented as mean values (M) and SD in case of parametric data and median and range for non-parametric data. A *p*-value < .05 will be considered statistically significant for all analyses. To correct for multiple testing the Benjamini-Hochberg procedure will be used [73].

#### Descriptive statistics

Demographic and clinical characteristics such as age at first baseline assessment, sex, height, weight, %body fat, comorbidities with CIRS, medication, years since diagnosis, use of walking aid and EDSS score, will be summarized in a table. For therapy adherence and training intensity, frequencies and percentages will be calculated.

#### Primary objective

Within-group paired analysis will be performed for whole brain atrophy measured with PBVC at three different time intervals (difference between baseline 1 and 2, difference between baseline 2 and post- intervention and difference between post-intervention and follow-up) using linear mixed models The analysis will be performed separately for the two different exercise programs. The analysis will be performed using an intention-to-treat method, including all randomized participants, regardless of adherence and measurement completion. Secondary, per protocol analysis will be performed for further exploration of the intervention effects. In addition, one model for the total group of participants with the two different exercise programs as a determinant, will be explored.

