### Exercise PRO-MS

In the proposed Exercise PRO-MS study an extensive set of neurodegenerative biomarkers will be used to investigate the effect of two patient-tailored exercise programs, i.e. PRT and high intensity interval training (HIIT) on neurodegeneration in people with PMS. Both resistance and endurance training might affect neurodegeneration but currently it is unknown whether one intervention is more beneficial than the other one. In the proposed study we will examine the effectiveness of both interventions on neurodegeneration in the PMS population.

The primary aim of this trial is:

To examine whether PRT and HIIT can slow down neurodegeneration in people with PMS. We expect that participants will benefit from both PRT and HIIT as compared to no training.

Additional objectives of the Exercise PRO-MS study are:
To determine whether PRT and HIIT can improve patient functioning in people with PMS.To explore the relationships between patient functioning on the one hand, and biomarkers related to neurodegeneration on the other hand.To determine the relative responsiveness of neurodegeneration outcome measures, and to explore effect sizes of between-intervention comparisons.To determine whether cardiovascular risk factors improve as a consequence of a PRT or a HIIT intervention.

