### Sample size calculation

Based on pre- and post-intervention measurements, paired analysis will be performed to examine the effect of exercise per type of intervention. Power calculation was performed using data from a previous study examining the effect of a 24-week progressive resistance training (group difference of 0.3 PBVC, standard deviation (SD) 0.5, estimated effect size 0.6) [7]. A sample size of 24 achieves 80% power with a significance level of 0.05. With an estimated drop-out of 15% we will include 30 participants per group.

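### Separate primary models for PRT and HIIT each use only half of the pre-randomisation run-in data; one model with a common week 0–16 mean would cut each arm's variance by (1 − rho)/4, with rho not given

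*Protocol article*

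**What the plan says.** All places are in the protocol article.

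- **Exercise PRO-MS (aims):** the target is each programme against no training: "We expect that participants will benefit from both PRT and HIIT as compared to no training". Between-programme effect sizes are an additional objective, to be explored.
- **Design and setting:** there is no untrained arm. The reference is each participant's own run-in: "In an extended baseline design, participants function as their own control reducing variance and increasing power". On timing: "After the second baseline measurement participants will be randomized to either the PRT or HIIT group".
- **Statistical analysis, Primary objective:** PBVC is analysed by linear mixed model over three intervals, "difference between baseline 1 and 2, difference between baseline 2 and post- intervention and difference between post-intervention and follow-up". The models are fitted by arm: "The analysis will be performed separately for the two different exercise programs". A combined model is secondary: "In addition, one model for the total group of participants with the two different exercise programs as a determinant, will be explored". Nothing is said about a run-in mean common to both arms.
- **Sample size calculation:** a paired analysis per programme, using "group difference of 0.3 PBVC, standard deviation (SD) 0.5, estimated effect size 0.6". This gives 24 evaluable per arm, and 30 enrolled to allow for 15% drop-out.

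**The concern.** Up to week 16 no one has been allocated, so the two arms are random halves of one untrained population. The week 0–16 PBVC has one expected value, not two. Separate models estimate that value twice, from about 30 people each, and each ignores the other half of the run-in scans.

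Two things are at stake. The first is precision on the primary contrast, in a trial with only 24 evaluable people planned per arm. The second is interpretation: a chance difference between the arms in the run-in interval feeds, in part, into each arm's result. Two separate p-values can then diverge for a reason unrelated to the programmes, while the only randomised comparison, PRT against HIIT, is left to an exploratory model.

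**Working it through.** **Inputs.** From the article: difference 0.3, SD 0.5, effect size 0.6, 24 evaluable and 30 enrolled per arm, significance level 0.05, roughly equal allocation, randomisation after week 16. Assumed, because the article does not give them: the within-person correlation rho between run-in PBVC (X) and training PBVC (Y), equal SD s in both intervals, and complete data. The last two are relaxed below.

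**The plan's own figure.** A two-sided paired t-test at 0.05 with effect size 0.3/0.5 = 0.6 needs n = 24 (power 80.4%; n = 23 gives 78.5%). The stated 24 reproduces. Inflating for 15% drop-out gives 24/0.85 = 28.2, so 29; the stated 30 is close.

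**Separate model, one arm.** The contrast is mean(Y) − mean(X), both from the n people in that arm:

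Var = 2(1 − rho)s²/n

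**Joint model with a common run-in mean.** The run-in mean comes from 2n people, and each arm's training mean is adjusted for its own run-in deviation:

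Var = [(1 − rho²) + (1 − rho)²/2]s²/n = (1 − rho)(3 + rho)s²/(2n)

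**Ratio, joint to separate:** (3 + rho)/4. The saving is 1 − (3 + rho)/4 = (1 − rho)/4, positive for every rho below 1. Numerical generalised least squares gave the same values, and a simulation of 100,000 replicates agreed (37.3%, 25.4%, 18.6% and 12.7% at rho = −0.5, 0, 0.25 and 0.5).

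| rho (assumed) | Ratio | Saving, complete data | Saving, 24 of 30 scanned at week 32 | People per separate arm giving the same precision as 30 per arm jointly |
|---|---|---|---|---|
| 0.75 | 0.9375 | 6% | 5% | 32 |
| 0.5 | 0.875 | 12.5% | 11% | 34 |
| 0.25 | 0.8125 | 19% | 16% | 37 |
| 0 | 0.75 | 25% | 22% | 40 |
| −0.5 | 0.625 | 37.5% | 35% | 48 |

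The last column is 30 divided by the ratio.

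**Why rho is open.** Stable differences between people in atrophy rate push rho up. The week-16 scan ends one interval and starts the next, so its measurement error enters the two with opposite signs and pushes rho down. Pure scan error would give −0.5.

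**Power at n = 24 per arm, difference 0.3.** This depends on what SD 0.5 describes.

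- If it is both the one-interval SD and the SD of the paired difference, then 0.5 = 0.5 × √(2(1 − rho)), so rho = 0.5. Power goes from 80% to about 86% (85–87%, depending on degrees of freedom).
- If it is the one-interval SD and rho = 0, the paired-difference SD is 0.5 × √2 = 0.707 and the effect size is 0.3/0.707 = 0.424. Power goes from 51% to about 64% (63–65%).

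**Unequal SDs.** At rho = 0, if the training-interval SD is 0.7 or 1.4 times the run-in SD, the saving is 34% or 17% instead of 25%.

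**Covariance.** A random-intercept model cannot represent a negative rho. With working rho 0 and true rho −0.5 the saving is 33%, not 37.5%.

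**Correlation between the arm estimates.** Under separate models it is zero. Under the joint model the shared covariance is (1 − rho)²s²/(2n), so the correlation is (1 − rho)/(3 + rho): 0.14 at rho = 0.5, 0.33 at 0 and 0.6 at −0.5.

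**The case against.** The strongest reply is that nothing here is an error. Separate paired models are valid, are unbiased for the same contrast and match the sample-size calculation. They also keep the two results independent: with a shared run-in mean, one chance-unfavourable run-in would flatter both programmes together. All of this stands, and it makes the point one of efficiency and reporting.

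A second reply is that a combined model is already planned: "one model for the total group of participants with the two different exercise programs as a determinant, will be explored". That answers less than it seems to. The model is exploratory, and no common run-in mean is stated. If it carries arm-specific run-in means and a full arm-by-interval term, it returns the same point estimates as the separate models. The gain comes only from the constraint.

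Several stronger readings are tempting but unsupported:

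- **A fixed saving of 19–38%.** That is the slice from rho = 0.25 to −0.5, with equal SDs and complete data. The article gives no rho, and the reading of its SD that yields rho = 0.5 gives 12.5%.
- **A trial already short of power.** This depends on whether SD 0.5 describes one interval or the paired difference; on the latter reading the planned 80% holds.
- **Run-in imbalance passing in full into each arm's effect.** In expectation only the fraction (1 − rho) of a chance run-in deviation carries through, because stable personal differences cancel within person.
- **Half of the precision being lost.** Half of the run-in observations go unused by each model; the loss in variance is much smaller.
- **A planned claim that one programme works and the other does not.** The article announces no such inference, and an exploratory between-arm comparison fits its stated aims.

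**Conclusion.** The point holds as an avoidable loss of efficiency. The article fixes separate per-arm models as primary, although its own timing of randomisation gives both arms the same expected run-in PBVC. Each model therefore estimates the only no-training reference from half the people who supply it.

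The variance saving forgone is (1 − rho)/4 per arm, given equal interval SDs and complete data. With rho unknown, that is about 6% to 38% for rho from 0.75 to −0.5, and 5% to 35% if 24 of 30 per arm are scanned at week 32. The top of the range needs an unstructured covariance. A reader might infer that the planned analysis is biased or invalid; the documents do not support that. The change is worth making because the gain is positive for any rho below 1 under these conditions and needs no new data.

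**What to change.** Replace the per-arm primary analysis with one linear mixed model on all randomised participants, specified as follows:

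1. Interval and arm-by-interval terms, with the week 0–16 mean constrained equal across arms.
2. An unstructured within-person covariance over the three intervals, so that a negative correlation between adjacent intervals can be fitted.
3. From this one model, the PRT contrast, the HIIT contrast and PRT minus HIIT, each with a confidence interval.
4. The separate-arm models kept as sensitivity analyses.
5. A sentence stating that the PRT and HIIT estimates share one run-in mean, so their errors are correlated and the two results are not independent confirmations.

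Any efficiency gain quoted should be given as (1 − rho)/4 with the assumed range of rho shown. The cost is analysis wording only: no extra scans, no extra participants and no change to the question asked of each programme. The price is the correlation between the two arm estimates. The change should be fixed before outcome data are analysed; the article reports that recruitment was still under way.
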